### Statistical analysis

Details of sample size calculation have already been published in the study protocol [11]. The sample size of 320 provides a power of 80% to detect a 15% absolute risk reduction in 28-day mortality from 40 to 25%. Categorical variables will be reported as numbers and frequencies and will be compared between the study groups using the chi-square test or Fisher’s exact test. Continuous variables will be reported as means and standard deviations or medians and the first and third quartiles (Q1–Q3) and will be compared between the study groups using the Student’s *t*-test or the Wilcoxon–Mann–Whitney test, as judged appropriate by normality testing using Shapiro–Wilk test. For serial measurements (such as SaO_2_:FiO2 ratio, fluid balance, and serial SOFA), we will test the change over time and the difference between the two study groups over time using generalized linear mixed effect models by considering the link function of logit to incorporate the binary nature of the response variable and link function of log for score outcomes, with no imputation for missing values. To adjust for multiple testing for secondary outcomes and subgroup analyses, we will use the false discovery rate (FDR) as described by Benjamini and Hochberg [15]. We will report associations as relative risk (RR) or hazard ratio (HR) with 95% confidence intervals (CI) or beta coefficient and 95% CI as appropriate. We will compare dyspnea scores and device discomfort scores using generalized linear mixed models, incorporating fixed effects of treatment, time, and the treatment by time interaction and random effects of patient and center. Tests will be two-sided and at the 5% significance level. All statistical analyses will be conducted using the SAS software version 9.4 (SAS Institute, Cary, NC, USA). The statistical analysis remains blinded to the research team until completion of primary outcome data on the study population and will be performed by the study biostatistician. A summary of the analysis plan is provided in Table 1.

**Table 1 Tab1:** Summary of the analysis plan

Variables	Intention-to-treat cohort	Per-protocol cohort
Baseline characteristics	No statistical comparisons	None
Intervention and co-interventions	Chi-square, Fisher’s exact test, Wilcoxon–Mann–Whitney test, *t*-test as applicable	None
Primary outcome	1. Primary analysis: chi-square or Fisher’s exact test. Report relative risk. 2. Secondary analyses: unadjusted Cox proportional analysis, KM curves, adjusted logistic regression	1. Primary analysis: chi-square or Fisher’s exact test. Report relative risk. 2. Secondary analyses: unadjusted Cox proportional analysis, KM curves, adjusted logistic regression
Secondary outcomes-categorical	Chi-square or Fisher’s exact test. Report relative risk	Chi-square or Fisher’s exact test. Report relative risk
Secondary outcomes-continuous	Generalized linear mixed models. Report beta estimate	Generalized linear mixed models. Report beta estimate
Safety outcomes and other variables	Chi-square or Fisher’s exact test. Report relative risk. For serial measurements, generalized linear mixed effect models	None
Subgroup analyses	Chi-square or Fisher’s exact test. Report relative risk. Tests of interaction	None
180-day follow-up	Chi-square or Fisher’s exact test for 180-day mortality. Report relative risk Generalized linear mixed models for EQ-5D-5L ad VAS. Report beta estimate	Chi-square or Fisher’s exact test for 180-day mortality. Report relative risk Generalized linear mixed models for EQ-5D-5L ad VAS. Report beta estimate

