**Fig. 1 Fig1:**
[figure not shown]
CONSORT flow diagram

*The intention-to-treat population* consists of all randomized patients and will be used for the primary analysis. All randomized patients will be included regardless of whether they receive or do not receive the allocated intervention. All patients randomized with suspected COVID-19 will remain in the study, even if they tested negative for COVID-19 after enrollment. Post-enrollment exclusion from the intention-to-treat analysis will be restricted to the withdrawal of consent to use trial data by the patient or surrogate decision-maker (SDM) or wrong randomization (for example, randomization of an ineligible patient in error). However, if the patient or SDM withdraws consent for trial participation but permits collection and use of data, the patient will be included in the intention-to-treat analysis. We plan to enroll additional patients to compensate for patients who are excluded post-randomization, so the sample size of 320 patients in the intention-to-treat cohort is reached.

*The per-protocol population* consists of all randomized patients who receive respiratory support as per the allocated group (helmet NIV in the helmet NIV group, and no helmet NIV in the usual care group). Patients will be considered to have received helmet NIV if the device was applied for 1 h or more.

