#### Intervention data

For each 24 h in the first 96 h, we will report in each group the details regarding helmet NIV (number of hours used, highest pressure support level, and PEEP). Throughout the first 28 days, we will document the number of days with helmet treatment (> 1 h) and the total hours of helmet NIV. Non-tolerance to helmet NIV is defined as the need to remove the helmet because of patient preference or evidence of clinical deterioration. We will document other reasons for discontinuation of the helmet NIV (clinical improvement, the need for intubation, helmet removal due to change in goals of care or death while on helmet). We will document respiratory support after discontinuation of helmet NIV (mask NIV, HFNO, other oxygen devices, intubation). Violations to the study protocol will be documented including the use of NIV helmet in the usual care group and lack of attempt to use helmet NIV in the intervention group (Supplement Table S2).

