#### Secondary outcomes

A detailed list of secondary outcomes with definitions has already been published and is outlined in Supplement Table S4. These secondary outcomes can be grouped as follows:
Mortality outcomes
ICU mortalityHospital mortalityEndotracheal intubation. We will document time to intubation, reasons for intubation as determined by the treating team (neurologic deterioration that is not attributed to sedation, persistent or worsening respiratory failure of NIV such as SaO2 < 88%, respiratory rate > 36/min, PaO_2_:FiO_2_ ratio < 100 or persistent requirement of FiO_2_ ≥ 70%, intolerance of mask or helmet NIV, airway bleeding, copious respiratory secretions, respiratory acidosis with pH < 7.25, hemodynamic instability, or significant radiological worsening). We will document mechanical ventilation parameters in the first 24 h after intubation (peak airway pressure, plateau pressure, PEEP in cm H_2_O), FiO_2_, tidal volume, and respiratory rate. We will also document oxygen rescue therapies during invasive mechanical ventilation (neuromuscular blocker infusion, recruitment maneuvers, inhaled nitric oxide, prone positioning, extracorporeal membrane oxygenation (ECMO)). We will report the percentage of patients who underwent tracheostomy.Continuous outcomes
ICU-free days at day 28Hospital length of stay (LOS)Invasive mechanical ventilation-free days at day 28Renal replacement therapy-free days at day 28Vasopressor-free days at day 28Safety outcomes
Skin injury at the nose, face, neck, and axillae, with the highest stage during the intervention period. We will use the stages as per the National Pressure Ulcer Advisory Panel [14]: stage I: non-blanchable erythema, stage II: partial thickness, stage III: full-thickness skin loss, and stage IV: full-thickness tissue lossBarotrauma, including pneumothorax, mediastinal air or subcutaneous emphysemaCardiovascular eventsDevice complications (such as helmet deflation or malfunction)Serious adverse events (SAEs)Follow-up study: There will be a follow-up of enrolled patients at day 180 about vital status, functional status (EuroQoL (EQ)-5D-5L), by an unblinded assessor, which is planned to be reported separately. For patients who have been discharged from the hospital before day 180, follow-up will be conducted by telephone.

We will also report protocol violations (Supplement Table S6).

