#### Analysis of secondary outcomes

Secondary outcomes will be compared in the intention-to-treat cohort only. Categorical outcomes will be compared in the intention-to-treat using a chi-square test. Results will be reported as RR with 95% CI. Continuous outcomes will be compared using generalized linear mixed models. Results will be reported as beta estimates with 95% CI.

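### Safety is compared by allocated group only, so any crossover or non-use would dilute harms caused by the helmet itself; no supportive table by treatment received is planned

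*SAP article*

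**What the plan says.** Table 1 (Statistical analysis) has one row for "Safety outcomes and other variables". The intention-to-treat column lists chi-square or Fisher's exact tests with relative risks, and mixed models for serial measurements. The per-protocol column reads 'None'. The same table gives per-protocol analyses for 28-day mortality, the secondary outcomes and the 180-day outcomes.

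The intention-to-treat cohort is grouped by allocation: "All randomized patients will be included regardless of whether they receive or do not receive the allocated intervention". The per-protocol cohort keeps patients whose support matches their group: "helmet NIV in the helmet NIV group, and no helmet NIV in the usual care group". Receipt is also defined: "Patients will be considered to have received helmet NIV if the device was applied for 1 h or more".

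Under Intervention data, the plan lists violations to be documented, "including the use of NIV helmet in the usual care group and lack of attempt to use helmet NIV in the intervention group". The same section collects helmet hours for each of the first four days, and helmet days and total helmet hours to day 28.

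The safety outcomes under Secondary outcomes start with "Skin injury at the nose, face, neck, and axillae, with the highest stage during the intervention period". They continue with barotrauma, cardiovascular events, device complications (helmet deflation is an example given) and serious adverse events. No analysis of these by treatment received appears in the document.

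**The concern.** Some of the listed harms can come only, or mainly, from wearing the helmet. A helmet cannot deflate on a patient who never wore one. Under grouping by allocation, such an event in a usual-care patient who was given a helmet is a usual-care event, and a helmet-group patient who never wore the device stays in the helmet denominator. Both pull the observed difference in helmet-caused harm towards zero. For harms that is the unsafe direction, because a small or non-significant difference may be read as no excess harm.

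The plan measures exposure and defines receipt of the helmet, but it does not link either to the harms that depend most directly on exposure.

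**Working it through.** **The plan's own figure.** The only design figure is for mortality: "The sample size of 320 provides a power of 80% to detect a 15% absolute risk reduction in 28-day mortality from 40 to 25" (per cent). With 160 per arm, power is 82.0% at two-sided 5% and 81.6% at the final level of 0.048, in reasonable agreement with the stated 80%. The figure does not bear on safety. It only fixes the arm size used below (320 at 1:1, so 160 per arm).

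**Inputs.** From the plan: 160 per arm and two-sided 5%. Assumed, because the plan gives no safety event, non-use or crossover rates: risk h with the helmet, risk b without it, non-use share u in the helmet arm, crossover share c in usual care. The model also assumes that non-users carry risk b and crossovers carry risk h.

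**Formulas.**
- Observed helmet-arm risk = h(1 − u) + b·u
- Observed usual-care risk = b(1 − c) + h·c
- Observed difference = (h − b)(1 − u − c)
- Power ≈ Φ(difference / SE − 1.96), where SE = √{[p₁(1 − p₁) + p₂(1 − p₂)] / 160}

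**Results for h = 15%, b = 5%.**

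| u and c (each) | Helmet arm | Usual care | Difference | RR | Power |
|---|---|---|---|---|---|
| 0% | 15.0% | 5.0% | 10 points | 3.0 | 86% |
| 5% | 14.5% | 5.5% | 9 points | 2.6 | 77% |
| 10% | 14.0% | 6.0% | 8 points | 2.3 | 67% |
| 20% | 13.0% | 7.0% | 6 points | 1.9 | 44% |

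For the 10% row, SE = √[(0.1204 + 0.0564)/160] = 0.0332, and 0.08/0.0332 − 1.96 = 0.45, so power is 67%. A pooled variance under the null gives 85%, 77%, 67% and 43% for the four rows, so the choice of formula hardly matters.

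**Rarer harm, h = 6%, b = 2%.** Power is about 45% even with full adherence and about 31% at 10% + 10%. The RR falls from 3.0 to 2.3 as before.

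**Event possible only under a helmet, h = 5%, b = 0.** The expected number of helmet events counted in usual care is 160 × c × 0.05: 0.4 at c = 5%, 0.8 at 10% and 1.6 at 20%. The counts are small, but each such event is one the comparator could not have produced.

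**Would the per-protocol cohort help?** No. By its definition that cohort leaves out crossovers and non-users and does not reassign them. A helmet deflation in a usual-care patient would drop out of the table altogether. Grouping by treatment received is needed to place it with the helmet.

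**The case against.** The other side has several sound points.

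- **Comparison by allocation is legitimate.** It estimates the effect of the assigned strategy on harms and is randomised. On safety the plan is consistent, since Table 1 agrees with the text: "Secondary outcomes will be compared in the intention-to-treat cohort only". This stands, and it is why the comparison should remain the main one. (Table 1 does conflict with that sentence by giving per-protocol analyses for other secondary outcomes. That is a separate matter to reconcile.)
- **Non-adherence is not forecast.** A reader might infer that the plan expects crossover and non-use. It does not say so. It names two violations to be recorded and gives no rate for either. With full adherence there is no dilution.
- **The argument does not cover the whole safety row.** A reader might conclude that every safety comparison is biased towards no difference. Usual care may include mask NIV, which could injure the nose and face, so non-adherence there might even hide a helmet advantage. Barotrauma, cardiovascular events and serious adverse events can also follow intubation in either arm.
- **Some transparency is already planned.** Helmet hours, non-tolerance, reasons for stopping and violations will be reported, so a reader could judge how much non-adherence lies behind a null result. That helps, but it does not place events by exposure.
- **An analysis by treatment received is confounded.** Patients who cross over, or who never get the helmet, are probably selected by severity. This limits how the table may be read, but a supportive table remains useful.

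The full protocol and supplement are not at hand and might contain exposure-based safety reporting. The point is therefore about what Table 1 fixes.

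**Conclusion.** The point holds in a limited form. Table 1 compares safety by allocation alone, and the document has no supportive analysis by treatment received. If crossover or non-use occurs, the difference in harms caused by the helmet itself is reduced to (1 − u − c) of its true value: 90% at 5% + 5%, 80% at 10% + 10%, 60% at 20% + 20%. The direction follows from algebra, given that non-users carry the unexposed risk and crossovers the exposed risk. The size cannot be taken from the plan, and all risks and rates above are assumptions. In the illustration at 10% + 10% the signal is weakened (RR 2.3, 8 points) but not erased.

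The documents do not support saying that the intention-to-treat safety comparison is an error, that dilution will happen, or that it affects cardiovascular events, serious adverse events or nose and face injury in a known direction. The primary analysis is untouched.

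**What to change.** Keep the intention-to-treat safety comparison as the main one. Before unblinding, replace 'None' with one pre-specified supportive table of device-related harms (device complications, neck and axillary skin injury, barotrauma during helmet use) by treatment received:

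- Group by helmet ever applied versus never, because an event can occur before the one-hour threshold is reached.
- Count events before first application as unexposed.
- Limit attribution to the period of helmet use, so that events after intubation are not charged to the helmet.
- Report device events per helmet hour, using the total hours already collected to day 28.

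Do not fill the cell with the existing per-protocol cohort.

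The cost is one extra table, largely from data already planned; event dates relative to helmet use must be available. The table is not randomised and is open to confounding by severity, so it should be labelled supportive and read alongside the allocated-group result.

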#### Analysis of primary outcome

The primary outcome will be compared in the intention-to-treat using the chi-square test. Results will be reported as RR with 95% CI. We will use an unadjusted Cox proportional hazard model as a secondary analysis tool, and the results will be reported as hazard ratio (HR) and 95% CI. We will use Kaplan–Meier survival function estimates to assess proportional hazards for categorical covariates. Moreover, we will be using the supremum test of the null hypothesis that the observed pattern of martingale residuals is not different from the expected pattern [16]. A very small *p*-value (≤ 0.05) suggests a violation of proportional hazards. Kaplan–Meier curves will be generated for the two study groups and a log-rank test will be used to compare distributions. Although imbalances in baseline characteristics are unlikely with the large sample size, we will conduct an adjusted logistic regression model to adjust for the following factors (defined a priori): enrolment center, respiratory support at baseline (mask NIV support versus others), PaO_2_:FiO_2_ ratio, body mass index > 30 kg/m^2^, age, APACHE II score, and time (time of enrolling the first half of the cohort versus the second half); the latter will be included to account for the changes in outcomes of COVID-19 patients during the pandemic.

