### Study population

All adult (adult ICU cut-off age) patients admitted to the ICU with suspected or confirmed COVID-19 by reverse transcription-polymerase chain reaction (RT-PCR) will be screened for eligibility. Inclusion criteria include acute hypoxemic respiratory failure (PaO_2_:FiO_2_ ratio < 200 despite supplemental oxygen with a partial/non-rebreathing mask at a flow rate of 10 L/min or above) with intact airway protective gag reflex and ability to follow instructions. Exclusion criteria include imminent intubation and the requirement for more than one vasopressor. A full list of inclusion and exclusion criteria is described in the published protocol [11]. Enrolled patients will be randomized using a concealed online system to helmet NIV with usual care or usual care alone at a 1:1 ratio. Usual care may include mask NIV, HFNO, or standard oxygen therapy. Randomization will be stratified by site. Helmet NIV will be delivered in pressure support mode, with initial settings of pressure support of 8–10 cm H_2_O, PEEP of 10 cm H_2_O with FiO_2_ of 100%, targeting flow rate of ≥ 50 L/min with an inspiratory rise time of 50 ms, and end flow/cycling off of 50% of maximal inspiratory flow. The settings can be adjusted according to the study protocol. The management of respiratory support in the usual care group including mask NIV is at the discretion of the treating team.

A flow diagram will be constructed according to the CONSORT guidelines (Fig. 1). We will report the number of patients who were screened, met inclusion or exclusion criteria, and were eligible but not enrolled with reasons for non-enrollment. We will report the number of patients who were randomized to each group, received the allocated intervention, withdrawn/lost-to-follow-up with reasons, and included in the final analysis.

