#### Interim analyses

The interim test statistics will be conducted for the primary outcome. Two formal interim analyses are planned when 33% and 67% of the sample size are reached. The trial may be stopped for safety (*p* < 0.01) or effectiveness (*p* < 0.001) both evaluating the primary outcome (28-day mortality) but there will be no plans to terminate the trial for futility. We will account for alpha spending by the O’Brien-Fleming method and the final *p*-value will be considered at 0.048 [20].

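### Randomisation is stratified by site but the primary chi-square test ignores site, so the test is conservative and its interval somewhat too wide if 28-day mortality differs between sites

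*SAP article*

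**What the plan says.** Under Study population, patients are allocated to "helmet NIV with usual care or usual care alone at a 1:1 ratio", and "Randomization will be stratified by site". Site is the only stratification factor named.

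Under Analysis of primary outcome: "The primary outcome will be compared in the intention-to-treat using the chi-square test". The result is an RR with 95% CI. The abstract says the same. Table 1 reads "Primary analysis: chi-square or Fisher’s exact test. Report relative risk". None of the three places mentions site.

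Centre appears in mortality only as part of a secondary analysis: "we will conduct an adjusted logistic regression model to adjust for the following factors (defined a priori", with enrolment centre first on the list. That model is introduced as cover against baseline imbalance. Elsewhere, centre is a random effect for the dyspnea and discomfort scores (Statistical analysis) and for EQ-5D-5L and VAS at 180 days.

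The article gives no reason for leaving site out of the primary test and no figure for mortality by site.

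**The concern.** Stratified allocation balances the arms within each site, so differences in mortality between sites largely cancel out of the treatment comparison. The crude chi-square and crude RR interval still count those differences as random error. Where sites differ, the standard error is then larger than the design warrants, the p-value too large and the interval too wide.

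At stake is the efficiency of the one analysis that decides the trial, and its coherence with the design. The plan already treats centre as worth adjusting for in several other analyses. The secondary logistic model does not close the gap: it does not set the primary p-value, and ordinary logistic regression gives an odds ratio, whereas the plan reports an RR.

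**Working it through.** **1. Reproduce the stated power.** The Statistical analysis section gives 320 patients (160 per arm at 1:1), 28-day mortality of 40% against 25%, and 80% power. It also says "Tests will be two-sided and at the 5% significance level"; under Interim analyses the final p-"value will be considered at 0.048".

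With pooled variance under the null, p̄ = (0.40 + 0.25)/2 = 0.325 and

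power = Φ{ [0.15·√160 − z·√(2·0.325·0.675)] / √(0.40·0.60 + 0.25·0.75) }.

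- Alpha 0.05: z = 1.960, so Φ{(1.897 − 1.298)/0.654} = Φ(0.916) = 82.0%.
- Alpha 0.048: z = 1.977, so Φ{(1.897 − 1.310)/0.654} = Φ(0.899) = 81.6%.

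For exactly 80% power the formula needs 152 per arm (304) at alpha 0.05 and 154 per arm (308) at 0.048. So 320 patients give the stated 80%, with a little to spare, for the unstratified test.

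**2. Why the crude test is conservative, by formula.** Under the null, with arms balanced within equal-sized sites whose risks are p_k, the true variance of the treatment difference is the crude variance multiplied approximately by

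r = 1 − Var(p_k) / [p̄(1 − p̄)],

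and the actual type I error is about 2Φ(−1.96/√r). Take 7 equal sites with mean risk 0.40, so p̄(1 − p̄) = 0.24:

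- Site SD 0 on the logit scale: r = 1, type I error 5.0%.
- SD 0.5: site risks 0.23 to 0.59, variance 0.0133, r = 0.945, √r = 0.972, type I error 4.4%.
- SD 1.0: site risks 0.11 to 0.75, variance 0.0433, r = 0.820, √r = 0.905, type I error 3.0%.

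The crude standard error of the difference is thus about 3% too large at SD 0.5 (1/0.972 = 1.03) and 10% at SD 1.0 (1/0.905 = 1.10).

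**3. Simulation of both tests.** 200,000 trials per setting, 320 patients, overall risks held at 40% and 25%, two-sided alpha 0.05. From the article: 320 patients, the two risks, stratification by site and 7 centres (the number in the abstract as of 1 August 2021). Assumed: the site SDs, permuted blocks of 4 within site, and site sizes, either equal or skewed (130, 70, 45, 30, 20, 15, 10). Ranges cover both sets of site sizes.

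| Site SD (logit) | Control risk across sites | Type I error, chi-square | Power, chi-square | Power, CMH by site | Gain (points) |
|---|---|---|---|---|---|
| 0 | 40% | 5.0% | 82.1–82.3% | 82.0–82.2% | about −0.1 |
| 0.3 | 26–52% | 4.7–4.8% | 82.3–82.5% | 82.5–82.9% | 0.3–0.4 |
| 0.5 | 18–59% | 4.4–4.5% | 82.8–82.9% | 83.6–84.1% | 0.8–1.2 |
| 0.8 | 10–69% | 3.6–4.0% | 83.2–83.6% | 85.2–86.5% | 2.0–2.9 |
| 1.0 | 7–75% | 3.1–3.5% | 83.6–84.1% | 86.4–88.1% | 2.8–4.1 |

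CMH type I error stays at 4.9 to 5.1% throughout. Monte Carlo standard errors are about 0.05 points for type I error, √(0.05·0.95/200,000), and 0.09 points for power, √(0.82·0.18/200,000). The simulated type I errors agree with step 2. Alpha 0.048 gives the same pattern.

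**The case against.** The strongest case for leaving the plan alone has four parts.

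- **No planned power is lost.** The 80% was computed for an unstratified comparison, and the chi-square keeps at least 82% at alpha 0.05 in every setting of the table. This stands. A reader might infer that the trial is underpowered or its primary p-value invalid, but the plan's own figures do not support that: the error can only be conservative, and the design target is met.
- **The effect depends on something the article does not report.** With no site differences nothing is forgone, and up to an SD of 0.5 the gain is about 1 point. Gains of 3 to 4 points need control mortality ranging from roughly 10% to 65–75% across sites. This stands too. A reader might take the test to be conservative as a matter of fact, but the documents support only the conditional statement.
- **Centre is already in a pre-specified secondary model, and an unadjusted primary test is a defensible convention.** True, but that model neither sets the primary p-value nor gives a stratified RR.
- **It is late to change the primary test.** By 1 August 2021, 252 patients were enrolled, beyond both interim points (0.33 × 320 = 106 and 0.67 × 320 = 214). The article does not say whether the looks took place, but any that did would have used the crude test. This calls for a statement and is no bar: the Background section keeps the SAP's authors blinded until recruitment ends and the database is locked, and the crude result would still be reported.

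A reader might also want age, APACHE II and PaO2:FiO2 moved into the primary analysis for a larger gain. That gain depends on prognostic strength the documents do not give, and the move would leave open how the promised RR is obtained. It is not part of this point.

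**Conclusion.** The mismatch between site-stratified randomisation and a primary test that ignores site is plain in the text. Its consequence is conditional. If 28-day mortality differs between sites, chi-square type I error falls below 5% (about 4.5% at SD 0.5, 3.1 to 3.5% at SD 1.0), the crude interval is somewhat too wide, and about 1 or 3 to 4 points of power respectively are forgone. If sites do not differ, the stratified test costs about 0.1 point.

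These figures assume 7 sites, blocks of 4, the two sets of site sizes shown and the listed SDs; only the number of sites comes from the article. The point concerns efficiency and coherence with the design. It is worth correcting because the correction is nearly free.

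**What to change.** Before unblinding:

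- Make the primary test a Cochran-Mantel-Haenszel test stratified by site, with the Mantel-Haenszel RR and its 95% CI.
- Keep the crude chi-square and crude RR as a named supportive analysis.
- Leave the covariate-adjusted logistic model as secondary.
- Align the abstract, Table 1 and Analysis of primary outcome.
- State which test any completed interim look used.

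If the team prefers to keep the crude test as primary, the lesser step is to give the reason and name the site-stratified test and RR as a sensitivity analysis.

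Cost: wording in three places and a short addition to the analysis program, with no extra patients or data. The one statistical drawback is that a site with patients in only one arm contributes nothing to the stratified test.

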**Methods:**

In this multicenter randomized trial of helmet noninvasive ventilation for COVID-19 patients, 320 adult ICU patients (aged ≥14 years or as per local standards) with suspected or confirmed COVID-19 and acute hypoxemic respiratory failure (ratio of arterial oxygen partial pressure to fraction of inspired oxygen < 200 despite supplemental oxygen with a partial/non-rebreathing mask at a flow rate of 10 L/min or higher) will be randomized to helmet noninvasive ventilation with usual care or usual care alone, which may include mask noninvasive ventilation, high-flow nasal oxygen, or standard oxygen therapy. The primary outcome is death from any cause within 28 days after randomization. The trial has 80% power to detect a 15% absolute risk reduction in 28-day mortality from 40 to 25%. The primary outcome will be compared between the helmet and usual care group in the intention-to-treat using the chi-square test. Results will be reported as relative risk  and 95% confidence interval. The first patient was enrolled on February 8, 2021. As of August 1, 2021, 252 patients have been enrolled from 7 centers in Saudi Arabia and Kuwait.

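### The primary 28-day mortality test is unadjusted although prognostic covariates are pre-specified; adjusting the primary estimate would raise power from about 82% to 86–91% if they are moderately strong, and by 1–2 points if they are weak

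*SAP article*

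**What the plan says.** In the SAP article, the abstract (Methods), Table 1 and the section Analysis of primary outcome all make the crude comparison primary: "The primary outcome will be compared in the intention-to-treat using the chi-square test", reported as a relative risk with 95% CI. Table 1 lists adjusted logistic regression among the secondary analyses.

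The adjusted model is introduced with "Although imbalances in baseline characteristics are unlikely with the large sample size, we will conduct an adjusted logistic regression model". Its factors are fixed in advance: centre, baseline support (mask NIV or other), PaO2:FiO2, BMI above 30, age, APACHE II, and first or second half of enrolment. The only further reason given concerns the last factor, as a guard against changing COVID-19 outcomes. Precision is not mentioned.

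On size, the Statistical analysis section states that the sample of 320 "provides a power of 80% to detect a 15% absolute risk reduction", with "28-day mortality from 40 to 25" per cent. It also says "Tests will be two-sided and at the 5% significance level", while Interim analyses says "the final *p*-value will be considered at 0.048". Study population states 1:1 randomisation stratified by site alone, so the design does not balance age, severity or oxygenation.

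**The concern.** The plan collects and names patient-level factors likely to predict death, then leaves them out of its one confirmatory comparison. In a mortality trial, adjusting for such factors narrows the interval and raises power even when the arms are perfectly balanced. The plan presents adjustment only as a guard against imbalance, which it considers improbable at this size. That misses the main benefit, and the statement about imbalance needs checking at 160 per arm. At stake is the precision of the primary result in a trial that has little power to spare.

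**Working it through.** **Inputs from the SAP.** 320 patients, 1:1, so n = 160 per arm; risks 40% and 25%; two-sided alpha 0.05, with a final threshold of 0.048 after two interim analyses. **Assumed, because the SAP gives no figure:** the prognostic strength of the covariates, expressed as R² (share of outcome variance explained) or a joint c-statistic.

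**1. The plan's own power.** The pooled risk is 0.325.
- Null SE = √(2 × 0.325 × 0.675 / 160) = 0.0524.
- Alternative SE = √((0.40 × 0.60 + 0.25 × 0.75) / 160) = 0.0517.
- Power = Φ[(0.15 − 1.96 × 0.0524) / 0.0517] = 82.0%; at alpha 0.048 it is 81.6%.

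The stated 80% is met (78.7% and 78.2% with a continuity correction).

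**2. Power with adjustment, by formula.** Both SEs are multiplied by √(1 − R²).

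| Assumed R² | Power, alpha 0.05 | Power, alpha 0.048 |
|---|---|---|
| 0 | 82.0% | 81.6% |
| 0.05 | 83.9% | 83.5% |
| 0.10 | 85.8% | 85.4% |
| 0.15 | 87.7% | 87.4% |
| 0.20 | 89.6% | 89.3% |
| 0.25 | 91.4% | 91.1% |

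**3. Check by simulation.** 4,000 trials per setting, 160 per arm, a normal prognostic score, and intercepts calibrated to marginal risks of 40% and 25%. The adjusted analysis is a standardised (marginal) estimate with an influence-function SE, at alpha 0.05.

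| Log-OR per SD | c-statistic | Crude power | Adjusted power | Variance reduction |
|---|---|---|---|---|
| 0.75 | 0.69 | 82.3% | 86.1% | about 9% |
| 1.0 | 0.74 | 82.1% | 88.8% | about 16% |
| 1.3 | 0.79 | 81.7% | 91.2% | about 22% |

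- As sample size: 320/0.91 − 320 = 32, 320/0.84 − 320 = 61 and 320/0.78 − 320 = 90 extra patients.
- Five covariates instead of one score, with a degrees-of-freedom-corrected SE: gains of about 4, 6 and 9 points at the same three strengths, and about 1 to 2 points at log-OR 0.35 to 0.5. Type I error was about 5% (4.2% to 5.6%).
- Wald test from a three-covariate logistic model at alpha 0.048: gains of 1.4, 4.1, 5.8 and 7.9 points at c = 0.63, 0.69, 0.74 and 0.78.

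**4. Chance imbalance at 160 per arm.** The standardised difference has SD √(2/160) = 0.112, so its 95% range is ±0.22.

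| Absolute standardised difference | One covariate | At least one of three (independent) |
|---|---|---|
| > 0.1 | 37% | 75% |
| > 0.2 | 7% | 20% |
| > 0.25 | 2.5% | 7% |

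For a factor present in half the patients, the 95% range of the difference between arms is ±1.96 × √(2 × 0.25/160) = ±11 percentage points.

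**5. Crude test conditional on imbalance.** For R² of 0.09 to 0.22 (risk slope 0.148 to 0.219 per SD), a 0.2 SD imbalance in the joint score shifts the risk difference by 0.030 to 0.044. Type I error is then 7.5% to 10%. At 0.1 SD it is 4.4% to 4.8%. With perfect balance it is 4.0%, 3.2% and 2.6% for R² of 0.09, 0.16 and 0.22. Over all allocations the rate is 5%.

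**The case against.** The best defence is that nothing the plan promises fails. The crude chi-square is valid under randomisation, matches the sizing, and is accompanied by a pre-specified adjusted analysis that readers will see. The dispute is only about which result ranks first. The gain rests on covariate strength that the SAP does not state, and entry criteria such as PaO2:FiO2 below 200 may narrow the covariates' range and weaken them. All of this stands; it makes the point one of efficiency and its size conditional.

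Three stronger readings are tempting and are not supported:
- *That the primary test is crude because the sample is called large.* The clause introduces the adjusted model. The SAP gives no reason for the crude primary test.
- *That the plan ignores these predictors.* They are in a secondary model for the primary outcome, in both the intention-to-treat and per-protocol cohorts.
- *That the crude test has an inflated false-positive rate.* The 7.5% to 10% applies only at a 0.2 SD imbalance in the joint score, which about 7% of trials reach or exceed. Error below 5% in balanced allocations offsets it.

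It is also fair to say that large imbalance on a given covariate is unlikely (2.5% above 0.25). The clause, however, sets no such threshold.

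The objection does not remove the case for change. The data are already collected, the relative-risk scale can be kept, and the gain does not depend on imbalance occurring.

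**Conclusion.** The point holds as one of efficiency. The primary test is valid and properly powered, but it gives up precision available from covariates the plan already names. If their joint c-statistic is 0.69 to 0.79 (about 10% to 25% of outcome variance), power would rise from about 82% to about 86–91%. If c is only about 0.60 to 0.63, the gain is 1 to 2 points. The SAP does not say which case applies, so no single figure for lost power can be quoted.

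The clause on imbalance is unsupported for modest differences at 160 per arm and defensible only for large ones. It also points to the wrong motive for adjusting, which is mainly precision.

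**What to change.** Before database lock, while the authors remain blinded to results:

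- Make the primary estimate the marginal relative risk, with the risk difference beside it because the trial is sized on an absolute reduction. Obtain both by standardising a logistic model with treatment and the patient-level factors already listed: age, APACHE II and PaO2:FiO2 as continuous terms, baseline support, and BMI.
- Take the two-sided p-value from that estimate and judge it against the plan's final threshold. Use a robust or influence-function SE with a small-sample correction: with five covariates and no correction, simulated type I error was 5.4% to 5.7% (Monte Carlo SE about 0.35 points).
- State a simple rule for missing covariates so that no randomised patient leaves the analysis.
- Report the crude chi-square and relative risk alongside.
- Delete the clause calling imbalance unlikely and give precision as the reason for adjusting.

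The cost is SAP wording and a few lines of SAS, with no new data. The downsides are small: the primary result would depend on a pre-specified working model, and the published chi-square would become supportive. If the sponsor prefers to keep the crude test primary, the clause should still go.
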